**Figure 1 figure1:**
[figure not shown]
Study procedure. PIMPmyHospital: Patients In My Pocket in my Hospital; SUS: System Usability Scale; UTAUT: Unified Theory of Acceptance and Use of Technology.

**Table 2 table2:** Study schedule.

		Study period and time point			
		Pretest (*–t*_12__)_	Enrolment/app implementation (*t*_0_)	Posttest (*+t*_6_)	Closeout
**Study procedures**					
	Recruitment		✓^a^		
	Eligibility screening		✓		
	Informed consent form		✓		
**Assessments**					
	Case report form (demographics)		✓		
	EMR^b^-based data	✓	✓	✓	
	App-based data		✓	✓	
	UTAUT^c^		✓		✓
	SUS^d^				✓

^a^✓: Performed.

^b^EMR: electronic medical record.

^c^UTAUT: Unified Theory of Acceptance and Use of Technology.

^d^SUS: System Usability Scale.

### Technology Acceptance Terminology and Definition

We use technology acceptance to refer to an initial acceptance of use, as recently defined by Nadal et al [25], to explicitly distinguish between the different temporal stages of technological acceptance. It refers to users’ first interactions with the app at the preadoption stage before sustained acceptance of its use in the postadoption stage.

### Outcomes and Measures

#### Primary Outcome: Time to Laboratory Access

The primary outcome will be the mean elapsed time in minutes between the delivery of the laboratory results and the caregiver accessing them, both before and after the implementation of the app.

#### Secondary Outcome: Technology Acceptance and Usability

The secondary outcomes will be the technology acceptance and usability of the app. The 8-construct, 31-item UTAUT [23] will be used to measure app acceptance and intention to use. This is a 5-point Likert-type scale (1: strongly disagree, 2: moderately disagree, 3: neutral [neither disagree nor agree], 4: moderately agree, and 5: strongly agree). Usability of the app will be measured using the SUS designed by Jordan [24]. According to the International Organization for Standardization, the SUS assesses effectiveness (ie, the ability of users to use the product), efficiency (ie, the effort to use the product), and satisfaction (ie, how the users felt when using the product). It comprises a 10-item questionnaire with 5 response options for each item based on their level of agreement, ranging from 1 (strongly disagree) to 5 (strongly agree). According to the scoring system by Jordan [24], for odd-numbered (1, 3, 5, 7, and 9) statements (the positively-worded items), the score contribution is equal to the scale position minus 1 (eg, strongly agree: 5–1=4). For even-numbered (2, 4, 6, 8, and 10) statements (the negatively worded items), the score contribution is equal to 5 minus the scale position (eg, strongly agree: 5–5=0). Each score contribution falls within the range of 0 to 4. Participants’ scores for each item are then added up together and multiplied by 2.5 to convert the original scores of 0-40 to 0-100. Although the scores range from 0 to 100, these are not percentages of usability. The higher the score, the better the usability. To obtain a SUS score of 100, the respondent must answer 5 to all odd questions and 0 to all even questions. The original SUS items are presented in Multimedia Appendix 1. When translating the SUS questionnaire from its original version to French [26], we replaced the general term “system” with the specific term *PIMPmyHospital*. Another secondary outcome will be the mean ED-LOS per patient measured from the point when patients are triaged in the ED to discharge from the ED, defined as patients leaving the ED, whether admitted to the intensive care unit or ward, transferred to another hospital for admission, discharged home, or those who left without being seen. These data will be extracted from the hospital administrative electronic database. Finally, we will determine whether specific alerts, such as a flashing icon or sound for reported pathological values of laboratory results, have an impact on the results.

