**Methods:**

This single-center study of nonequivalent pre- and posttest comparison group design will be conducted before and after the implementation of the app in a tertiary pediatric ED in Switzerland. The retrospective period will cover the previous 12 months, and the prospective period will cover the following 6 months. Participants will be postgraduate residents pursuing a ≤6-year residency in pediatrics, pediatric emergency medicine fellows, and registered nurses from the pediatric ED. The primary outcome will be the mean elapsed time in minutes from delivery of laboratory results to caregivers’ consideration by accessing them either through the hospital’s electronic medical records or through the app before and after the implementation of the app, respectively. As secondary outcomes, participants will be queried about the acceptance and usability of the app using the Unified Theory of Acceptance and Use of Technology model and the System Usability Scale. ED length of stay will be compared before and after the implementation of the app for patients with laboratory results. The impact of specific alerts on the app, such as a flashing icon or sound for reported pathological values, will be reported.

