### Previous Work

Targeted interventions to reduce the postanalytical TAT phase may contribute to shortening ED-LOS, but mobile digital health solutions to achieve this goal are scarce. In a previous study [15], we described the user-centered development and early technology acceptance evaluation of a mobile app called “Patients In My Pocket in my Hospital” (*PIMPmyHospital*). The app was designed to help ED caregivers obtain relevant information in real time for the patients they care for, including laboratory and imaging results. The app also offers an end-to-end encrypted chat to provide a remote communication channel between caregivers caring for the same patients. In a randomized controlled pilot trial [16], the time required for ED physicians and nurses to review laboratory results after their release was significantly reduced by 92% using the app compared to the usual procedure in a semisimulated model. However, the potential effectiveness of this app in mitigating ED-LOS by taking cognizance of laboratory results in a shorter time frame than usual remains to be evaluated in daily clinical ED practice.

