## Methods

### Study Design

We will conduct an 18-month, single-center, nonequivalent comparison group, pre-post study. We will compare the control and experimental groups on outcome measures before (12-month period) and after (6-month period) the implementation and use of the app. This study protocol adheres to the Standard Protocol Items: Recommendations for Interventional Trials 2013 Checklist [18]. All data will be deidentified. The study will be conducted according to the principles of the Declaration of Helsinki [19] and Good Clinical Practice guidelines [20]. It is our intention to present these at scientific congresses and to publish the results in an international peer-reviewed journal, irrespective of the magnitude or direction of effect. Only deidentified data will be available to researchers for analysis. The study is registered at ClinicalTrials.gov on September 28, 2022 (NCT05557331).

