### Setting

The study will take place in the pediatric ED of a tertiary referral and major trauma hospital in Switzerland, with an annual volume of 35,000 visits. This should represent approximately 16,600 visits over the 6-month prospective intervention period, of which approximately one-half could potentially benefit from laboratory tests. The ED has 14 centrally monitored treatment rooms, a resuscitation room, a 5-bed short-term observation room (ie, <24 hours), a plaster room, a hypostimulation room, and a dedicated interview room. The patient population consists of local children from birth to 16 years of age with medical, surgical, and traumatology emergencies, as well as transfer cases from other hospitals in Switzerland or children located in neighboring France.

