### The PIMPmyHospital Mobile App

Information regarding the app has been published previously [16]. In brief, the app was developed iteratively following a user-centered approach starting with the identification of the main functionalities that meet end-user needs [15]. The system operates on a client-server architecture. Four microservices developed on the Java Spring Boot framework ensure (1) transmission of patient information, (2) access to real-time laboratory results, (3) the trigger of push notifications, and (4) exchange of information between caregivers through an instant messaging system. These microservices exchange information with the front end developed in the Angular and Ionic frameworks through a restful app programming interface. Patient medical data are not stored on the app itself, but in the institution’s EMR on secure servers to which the app connects. The exchange of data between the app and these servers is secured by the use of JSON web tokens obtained during the authentication of caregivers through a Keycloak identity and access management solution. User authentication on the device relies both on a login password and a specific certificate installed on the user’s device. The app runs on Google’s Android and Apple’s iOS operating systems.

The app’s interface features a home page with a personalized view of the patients that each caregiver is taking care of, together with associated information (eg, patient identity, time since admission, and patient’s geospatial location within the ED) and clickable actions next to them [16]. In particular, dropdown contextual tabs provide real-time access to laboratory results retrieved from the hospital patient’s EMR. Visual push notifications occur as soon as new results are made available. The entire patient management process is available to the caregiver in the palm of their hand and can be accessed at any time while on the go, hence the app’s name “Patients in my Pocket.”

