### Conclusions

Our intervention can serve as a foundation for a broader implementation of supportive mobile apps for in-hospital caregivers to improve the timely availability of EMR-derived results and the efficiency of care by reducing therapeutic TAT and ED-LOS.

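### ED-LOS is compared before and after the app with no concurrent comparator, a full year against November–April, so drift and season pass straight into the apparent app effect

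*Protocol article*

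**What the plan says.** The Secondary Outcome section of the protocol article defines the endpoint: "Another secondary outcome will be the mean ED-LOS per patient measured from the point when patients are triaged in the ED to discharge from the" department. Leaving the ED includes admission, transfer, discharge home and leaving without being seen, and the data come from the administrative database. That section names no comparator.

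The comparison itself is fixed in the abstract (Methods): "ED length of stay will be compared before and after the implementation of the app for patients with laboratory results". Study Design confirms the frame: "We will conduct an 18-month, single-center, nonequivalent comparison group, pre-post study". The Results section dates the pre-period 31 October 2021 to 31 October 2022 and the post-period 1 November 2022 to 30 April 2023.

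Statistical Analysis lists nine covariates, among them triage acuity, workload and month, but for time to laboratory access and not for ED-LOS. Limitations names volunteers' motivation and the pediatric setting. It does not name change over time.

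On volume, Setting gives 35,000 visits a year and about 16,600 in the intervention period, "of which approximately one-half could potentially benefit from laboratory tests".

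On what is delivered, Previous Work says: "The app was designed to help ED caregivers obtain relevant information in real time for the patients they care for, including laboratory and imaging results". It also says: "The app also offers an end-to-end encrypted chat to provide a remote communication channel between caregivers caring for the same patients". The app section lists, among the app's services, "exchange of information between caregivers through an instant messaging system", and shows patient location on the home page.

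**The concern.** ED-LOS depends on crowding, staffing, bed availability and winter case-mix as well as on how soon a result is read. A comparison of one calendar stretch with another, in tested patients only, gives no view of how the department moved for reasons unrelated to the app. Two distortions are possible:

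- **Year-to-year drift.** The second period may simply be busier or quieter than the first.
- **Season.** The pre-period averages over all months, while the post-period holds only November to April.

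Either could produce an apparent benefit or hide a real one. This matters because the Conclusions section looks ahead to improving "the efficiency of care by reducing therapeutic TAT and ED-LOS", and Previous Work presents a fall in ED-LOS through earlier laboratory review as the question still open.

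**Working it through.** **The plan's own figures.** The article gives no SD, effect size or sample size for ED-LOS. Its 5253 patients belong to the primary outcome and reproduce exactly: 85 per group × 2 = 170; design effect 1 + (300 − 1) × 0.1 = 30.9; 170 × 30.9 = 5253. That figure does not bear on this point. The rest is illustration under stated assumptions.

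**Inputs.** From Setting: 35,000 visits in the pre-year, 16,600 in the post-period, and about one-half with laboratory tests. The one-half is an assumption, since Setting says only that such patients could benefit from tests. It gives 17,500 tested visits before and 8,300 after, and the same numbers untested.

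**1. What the planned contrast estimates.** Let δ be the app effect, d the shared drift between years, s the November–April minus May–October difference in mean ED-LOS, and w the share of pre-period visits that fall in May–October.

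Expected (post − pre) = δ + d + w·s

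Drift enters with coefficient 1. If 16,600 also holds for November–April of the pre-year, w = (35,000 − 16,600)/35,000 = 0.526. For assumed s of 5, 10 and 20 minutes, the season term is 2.6, 5.3 and 10.5 minutes.

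**2. How easily drift looks like an effect.** Assume independent visits and a common SD. In SD units:

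SE = √(1/17,500 + 1/8,300) = 0.0133

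With δ = 0, the probability of two-sided significance at 5% is Φ(d/SE − 1.96) + Φ(−d/SE − 1.96):

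| Shared drift d | Probability |
|---|---|
| 0.02 SD | 0.32 |
| 0.05 SD | 0.96 |
| 0.10 SD | about 1.00 |

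Clustering would lower these probabilities but would not remove the bias.

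**3. What a comparator would give.** With L for tested and N for untested visits, restricted to November–April in both periods:

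Difference-in-differences = (δ_L + d_L) − (δ_N + d_N)

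If d_L = d_N, the drift cancels, and season is removed by the matching. An assumed 10-minute fall in every patient from better bed flow then gives −10 in the simple contrast and 0 here.

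**4. Precision.** The detectable change at 90% power is 3.24 × SE.

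- Full pre-year: 0.043 SD for the planned contrast and 0.043 × √2 = 0.061 SD for the difference-in-differences (0.062 SD if the tested share is 40% or 60%).
- Season-matched, assuming 16,600 visits in each November–April: SE = √(2/8,300) = 0.0155, so 0.050 SD for the simple contrast and 0.050 × √2 = 0.071 SD for the difference-in-differences.

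Clustering would enlarge all of these, but the numbers of visits are ample.

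**The case against.** **The design is declared openly.** The article calls itself a nonequivalent pre-post study with an exploratory aim, and ED-LOS is secondary. That stands, and it limits the weight of the point. It does not make the estimate robust to drift.

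**An ED-LOS model belongs in the analysis plan.** The absence of a model is not counted here. The population and the before/after contrast are stated in the article, and these are what leave drift unchecked.

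**The whole app is the intervention.** This objection is right. The abstract's Objective and the Objectives section ask about implementing the app, so messaging and patient location are part of what is tested. A reader might infer that the bundle invalidates the ED-LOS result, or that the protocol commits itself to crediting any fall to faster laboratory access. The documents do not support either reading. The Strengths section says only that a shorter turnaround might go with a shorter stay, and Conclusions names turnaround and ED-LOS side by side. Only Previous Work suggests the laboratory route, and the bundle limits that suggestion alone. Imaging appears in Previous Work but not in the app section's list of services.

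**Untested patients are an imperfect comparator.** This also stands. They use the same app functions, may gain from reduced crowding, may have a different trend, and presumably include most patients who left without being seen. These reasons keep the contrast supportive and narrow its reading. They are not a case for having no check at all.

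**Conclusion.** The point holds for drift and season. As stated, the ED-LOS comparison cannot separate an app effect from an ED-wide change between the periods, and the unequal calendar adds a seasonal term of about 0.53 times the seasonal difference in mean stay. The actual size is unknown because the article gives no ED-LOS mean, SD or trend. The figures above rest on an assumed one-half tested share, independent visits, a common SD, and 16,600 visits in November–April of both years. The direction could favor or disfavor the app.

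The simple result can be read as the change associated with implementing the whole app plus any change over time. The proposed contrast would show whether the change was shared with untested visits. It would not prove the laboratory mechanism, which would further require that the other functions act equally in both groups and that test ordering is unchanged. The point concerns a secondary outcome and calls for a supportive analysis and clearer wording.

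**What to change.** 1. Prespecify a supportive ED-LOS analysis: the November 2022–April 2023 minus November 2021–April 2022 change in visits with laboratory results, less the same change in visits without. Exclude patients who left without being seen from this contrast, and adjust for triage acuity and workload.
2. State that it is a check for shared drift and assumes parallel trends.
3. Describe the simple before/after ED-LOS result as the change associated with the whole app plus any change over time, and add change over time to Limitations.

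**Cost.** ED-LOS already comes from the administrative database, and restricting to tested patients already requires a laboratory flag. The extract must be widened to untested visits (roughly half, by assumption) and must carry acuity and workload. Data Collection says that no other patient-level data will be collected, so that statement needs to be reconciled with the wider extract.

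**Downsides.** Precision falls by a factor of √2 relative to the season-matched simple contrast. The contrast may understate the benefit if other app functions or shorter queues also help untested patients. Adjusting for workload may remove any benefit that acts through reduced crowding, so an unadjusted version should be shown beside it.

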### Statistical Analysis

The association of app use with the time between delivery of the laboratory results and their access by caregivers will be assessed using generalized estimating equations with an exchangeable correlation structure to account for the nested structure of the outcome (ie, time) within the physicians. To account for potential differences in case-mix and physician characteristics, we will use multivariable generalized estimating equations. The covariates will be as follows: (1) the triage acuity scale, (2) type of pathology (medical, surgical-traumatological, psychiatric), (3) experience of the caregiver expressed in years since certification, (4) patient age, (5) patient sex, (6) workload represented by the number of patients present in the emergency room, (7) time of day or night, (8) day of the week, and (9) month of the year (seasonal variability). To account for the possible effect of exogenous factors that would impose an asymmetry in the data (skewness on the right) by extending the awareness of laboratory results, we will identify these factors as the study progresses prospectively and take them into account in the final analysis. The same analyses will be performed for the nurses. We will carefully monitor and evaluate through descriptive analyses any differences between nurses’ and physicians’ frequency access to laboratory results. If the target sample size cannot be reached, we will first extend the prospective data collection period by 3 months (deemed ethically acceptable as not impacting patients) or present only the results of qualitative user experience interviews.

For the technology acceptance self-administered survey questionnaire, scores on the 8 technology acceptance constructs will be described using descriptive statistics. Items on the SUS questionnaire will be described using frequencies. Analyses will be carried out using R software (R Core Team) [27]. All statistical tests will be 2-sided, with an α risk of .05.

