## Results

Retrospective laboratory data will be arbitrarily collected from October 31, 2021, to October 31, 2022. Prospective data will be collected from the start of enrollment on November 1, 2022, through April 30, 2023. We anticipate an analysis of the results by mid-2023 and expect the results to be published in late 2023.

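### ED length of stay is set to be compared between a full calendar year and a November–April period, and the month adjustment is written only for time to access

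*Protocol article*

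**What the plan says.** **Windows.** Study Design applies one pair of windows to the outcome measures in general: "We will compare the control and experimental groups on outcome measures before (12-month period) and after (6-month period) the implementation and use of the app". The Results section dates them: "Retrospective laboratory data will be arbitrarily collected from October 31, 2021, to October 31, 2022" and "Prospective data will be collected from the start of enrollment on November 1, 2022, through April 30, 2023".

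**ED-LOS.** The section on secondary outcomes states: "Another secondary outcome will be the mean ED-LOS per patient". It runs from triage to leaving the ED, with data from the hospital's administrative database. The Abstract (Methods) adds the contrast and the population: "ED length of stay will be compared before and after the implementation of the app for patients with laboratory results". No model, test or covariate is named for this outcome.

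**Seasonal adjustment.** Statistical Analysis sets a multivariable generalized estimating equations model for the time from delivery of results to access. Its ninth covariate is "month of the year (seasonal variability". The section repeats the model for nurses. It then turns to descriptive summaries of the acceptance and usability questionnaires and does not return to ED-LOS.

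**The concern.** The authors treat season as a source of variation worth adjusting for in one outcome. A second outcome, measured over the same unequal windows, gets a plain before/after contrast. The pre period contains every calendar month and the post period only November to April. If ED-LOS differs between the two halves of the year, the contrast picks up that difference as if the app had caused it. Longer winter stays would hide a real shortening; shorter winter stays would produce a false one. More visits do not cure this, and there is no concurrent control group to reveal it.

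ED-LOS is among the listed study outcomes. Previous Work says that the app's effect on it is still to be evaluated in daily practice, and the closing Conclusions name its reduction, together with that of turnaround time, as a route to more efficient care.

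**Working it through.** The article gives no ED-LOS calculation to reproduce. Its one calculated figure, the sample size of 5253, belongs to time to access. It reproduces: 85 per group for 0.5 SD at 90% power and two-sided 5%, so 170 in total, times a design effect of 1 + (300 − 1) × 0.1 = 30.9, gives 5253. It has no bearing on this point.

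**1. Calendar content of the windows** (dates from Results)
- Pre: 31 October 2021 to 31 October 2022 = 366 days. November–April: 30 + 31 + 31 + 28 + 31 + 30 = 181. Remainder: 1 day (31 October 2021) + 184 days (May–October 2022) = 185, and 185/366 = 50.5%.
- Post: 1 November 2022 to 30 April 2023 = 181 days, all in November–April.

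**2. The same share by visits** (volumes from Setting)
- 16,600 visits in the six intervention months out of 35,000 a year: w = 16,600/35,000 = 0.474.
- Share with no post-period counterpart: 1 − w = 0.526.
- These are all visits, whereas ED-LOS is restricted to patients with laboratory results. Using 0.526 assumes that the seasonal split is the same in that subgroup.

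**3. Bias of the crude contrast**

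Let W and S be the mean ED-LOS without the app in November–April and May–October, d = W − S, and e the true shortening. Assume that the seasonal pattern is the same in both years.
- Pre mean = wW + (1 − w)S
- Post mean = W − e
- Pre minus post = e − (1 − w)d

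The contrast is therefore off by (1 − w)d: 0.505d by days, 0.526d by visits.

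**4. Illustrative sizes.** The article gives no value for d; those below are assumptions.

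| Assumed d (min) | By days (min) | By visits (min) |
|---|---|---|
| 5 | 2.5 | 2.6 |
| 10 | 5.1 | 5.3 |
| 20 | 10.1 | 10.5 |
| 30 | 15.2 | 15.8 |

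A negative d gives the same sizes with the sign reversed.

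**5. Matched months.** 1 November 2021–30 April 2022 against 1 November 2022–30 April 2023 is 181 against 181 days, and the month-mix term becomes 0.

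**6. Price in precision.** Take equal variances, independent visits, the same winter volume in both years and the same laboratory share in all months. The variance ratio of matched to unmatched is (1/16,600 + 1/16,600) / (1/35,000 + 1/16,600) = 0.0001205/0.0000888 = 1.357. The standard error rises by a factor of √1.357 = 1.16, about 16%.

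**The case against.** The strongest reply is that the article is silent on how ED-LOS will be analysed. It does not say that the comparison is unadjusted. It words the primary outcome in the same way, as a mean before and after implementation, and then gives it a fully adjusted model. Covariates for a secondary outcome are commonly left to an analysis plan, which is not shown. This stands against the stronger reading: a reader might infer that an unadjusted, biased ED-LOS analysis has been chosen, and the document does not support that. It does not remove the point, because the unequal windows are stated, they are applied to the outcome measures generally, and the month covariate is tied to one named outcome. The clause on exogenous factors in Statistical Analysis does not help, since it concerns delayed awareness of laboratory results.

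Second, the size is unknown: d could be near zero, and 0.526 comes from all visits. Both stand, so the minutes above are illustrations only.

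Third, the retrospective dates in Results refer to laboratory data, while ED-LOS comes from the administrative database. This carries little weight: Study Design applies the 12- and 6-month windows to outcome measures, and ED-LOS is limited to patients with laboratory results.

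Fourth, one winter against another is still an uncontrolled comparison. True. Matching removes the month mix and nothing else.

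Fifth, the weight of ED-LOS can be overstated. It is secondary, the Objective in the Abstract is exploratory, and the efficiency statement rests on turnaround time as well. The primary outcome, its model and the sample size are untouched.

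**Conclusion.** The point holds in a limited form. As stated, the ED-LOS contrast confounds the app with season, because about half of the pre-period (50.5% of days; about 53% of visits if the all-visit volumes carry over to patients with laboratory results) has no post-period counterpart. The bias is about 0.5d, for example about 5 minutes if d were 10. Its size and direction cannot be derived from the document. The result also assumes that the seasonal pattern is alike in the two years.

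A reader might also infer that ED census should be kept out of any ED-LOS model because it partly results from length of stay. The document does not support a flat rule: census also reflects patient inflow, and the plan already lists it as the workload covariate for the primary outcome. That choice can be argued separately.

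**What to change.** State one of the following for ED-LOS:
- the contrast is 1 November 2021–30 April 2022 against 1 November 2022–30 April 2023, with the remaining pre-period months shown descriptively; or
- the month covariate in Statistical Analysis also applies to ED-LOS. With separate month terms, the app effect then rests essentially on the six overlapping months.

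Statistical Analysis allows a 3-month extension of prospective collection. The rule should therefore read: the same calendar months as the final post window.

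Further case-mix adjustment (triage level, type of pathology, age, sex) should be promised only if those data will exist. Data Collection says that no clinical characteristics of patients will be gathered, while Statistical Analysis lists them as covariates. The two sections must be reconciled.

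Cost: matching is a change of wording and needs only visit dates. About half of the retrospective visits leave the contrast, with the loss of precision shown above, and differences between the two winters stay uncontrolled. The report should say so.
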